#### 2.11.2. Brief Advice

The brief advice will be consensual and provided by Family and Community Medicine specialists. It will be carried out in line with the guidelines established in the comprehensive plan against smoking in Andalusia, the integral smoking plan (PITA) [24]. Advice should be brief, opportunistic, personalised and clear (recommendation A). The strategy of this advice follows the mnemonic rule of the “5 As” (in Spanish): find out, advise, appreciate, help, and agree, the appropriate follow-up plan depending on the assigned arm, taking into account that the smokers participating in this study should be in the determination-action phase of the stages of change [10].

#### 2.11.3. Pharmacological Treatment with Cytisinicline

Treatment with cytisinicline of 1.5 mg tablets will be carried out by APHS physicians in order to meet the criteria established for its prescription, with clinical variables being recorded in the DIRAYA computer programme. In Spain, the cytisinicline manufacturers are Aflofarm (Pabianice, Poland) and Adamed (Pieńków, Poland), who indicate in the technical sheet that the patient should avoid smoking no later than the fifth day of treatment. In case of failure, it must be discontinued and may be resumed after two months. According to the datasheet, the duration of treatment (ingested) is twenty-five days. The treatment regimen [17] is shown in Table 4.

### 2.12. Participant Chronology and Schedule of Visits

All participating smokers will be followed up, either in person or by telephone, according to the plan established in this study and at the visits indicated below (Figure 1):-Selection visit (Day 0): FACE-TO-FACE. The potential participant is proposed to participate in the study. A check is made to ensure that the patient has no medical or other history that might contraindicate the prescription of physical exercise. The patient receives the information and signs the informed consent form if he/she wishes to be included in the study.-Visit 0 (Day 0): FACE-TO-FACE. Baseline data are collected on the previously mentioned variables. The necessary criteria for prescription are completed. The drug is prescribed to be approved within 24h, and a treatment start date is set.-Visit 1 (Day 7 ± 2): TELEPHONE. Data are collected, and the participant is asked if there are any problems with the motivation to continue.-Visit 2 (Day 30 ± 4): FACE-TO-FACE. Data are collected, and questions are asked if there have been any problems with the physical exercise, motivating for its continuation.-Visit 3 (Day 60 ± 7): FACE-TO-FACE. Data are collected, and questions are asked if there have been any problems with the physical exercise, motivating for its continuation.-Visit 4 (Day 90 ± 7): FACE-TO-FACE. Data are collected, and a question is asked as to whether there have been any problems with the physical exercise, motivating the patient to continue.-Visit 5 (Day 180 ± 15): FACE-TO-FACE. Data are collected, and a question is asked as to whether there have been any problems with the physical exercise, motivating the patient to continue.-Visit 6 (Day 365 ± 30): FACE-TO-FACE. Data are collected.

### 2.13. Statistical Analysis Plan

For the statistical analysis, the R programming language and its IDE (Integrated Development Environment) will be used: RStudio, in its most updated version.

Initially, a descriptive analysis of the baseline characteristics of the study population will be carried out using median and interquartile ranges for quantitative variables and absolute and relative frequencies for categorical variables.

To compare groups by bivariate analysis, Wilcoxon, Chi-square or Fisher tests will be used, as appropriate. Causal inference between intervention and outcomes will be made through multivariate analysis using logistic regression for the dichotomous variable “Smoking cessation” and linear regression for the variable “Number of cigarettes”, adjusting for potential confounders.

All analyses shall be conducted on an intention-to-treat basis, and no missing data shall be imputed.

Statistical significance will be established at a *p*-value < 0.05. Further analyses, including sensitivity and subgroup analyses, will be conducted to explore the robustness and generality of the findings.

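### For the quantitative outcomes, the plan names only one-record-per-person methods with no analysis visit and no imputation; read as a 12-month comparison this is a completers' analysis that leaves earlier visit data unused

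*Protocol article*

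**What the plan says.** Section 2.9 of the protocol article lists, besides smoking cessation, five quantitative outcomes: cigarettes per day, blood pressure, heart rate, weight and BMI.

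Section 2.12 schedules a telephone contact on Day 7 and five face-to-face follow-up visits: "Visit 2 (Day 30 ± 4): FACE-TO-FACE. Data are collected", "Visit 3 (Day 60 ± 7): FACE-TO-FACE. Data are collected", "Visit 4 (Day 90 ± 7): FACE-TO-FACE. Data are collected", "Visit 5 (Day 180 ± 15): FACE-TO-FACE. Data are collected" and "Visit 6 (Day 365 ± 30): FACE-TO-FACE. Data are collected". It does not itemise which variables are recorded at each visit.

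Section 2.13 gives the methods: "To compare groups by bivariate analysis, Wilcoxon, Chi-square or Fisher tests will be used, as appropriate". It adds logistic regression for cessation and "linear regression for the variable" counting cigarettes. No regression is named for weight, BMI, blood pressure or heart rate, so only the Wilcoxon test fits them. No analysis visit is given for any of the five, and no method that links a person's visits is named. The section continues: "All analyses shall be conducted on an intention-to-treat basis"; the same sentence excludes imputation.

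The limitations section expects some losses and relies on the intention-to-treat analysis, together with telephone follow-up, to reduce them.

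**The concern.** Each named method takes one independent record per person. The title and Section 2.3 point to 12 months, though for cessation, so the natural reading for the quantitative outcomes is a comparison at Day 365. With imputation excluded, a participant seen on Days 30, 60, 90 and 180 but not on Day 365 then contributes nothing. This fits poorly with the intention-to-treat statement, and it cannot do what the limitations section expects of that analysis.

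Two things are at stake. One is precision, in a trial that Section 2.3 already cuts from 289 to 75 per arm. The other is bias, if people leave because of their earlier smoking or weight and do so differently by arm. That is plausible, because only the experimental arm is prescribed the progressive exercise programme.

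**Working it through.** **Inputs from the protocol article:** 75 per arm (Section 2.3); five face-to-face follow-up visits (Section 2.12); one-record methods and no imputation (Section 2.13). The article gives no figure for a quantitative outcome to reproduce, and no dropout rate or within-person correlation.

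**Assumptions:** loss of 20% to 40% by Day 365 and correlation of 0.5 to 0.8 in the analytic check; 25% to 29% missing at Day 365 and adjacent-visit residual correlation of 0.7 to 0.8 in the simulation.

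**1. Who is left at Day 365.** Completers per arm = 75 × (1 − loss): 75 × 0.8 = 60; 75 × 0.7 = 52.5; 75 × 0.6 = 45.

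**2. What the earlier visits recover, by hand.** Suppose a proportion p is lost, everyone lost was last seen on Day 180, and the Day 180 to Day 365 correlation is r. Using Day 180 only, the maximum-likelihood variance of the Day 365 mean is σ²[(1 − r²)/(n(1 − p)) + r²/n]. Completers only give σ²/(n(1 − p)). The ratio is 1 − p·r². For p = 0.25 and r = 0.7 it is 1 − 0.25 × 0.49 = 0.88.

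**3. All five visits, loss spread evenly over the four intervals.** The information matrix is the sum, over dropout patterns, of the number of people times the inverse covariance of the visits they attended. The last diagonal element of its inverse is the variance of the Day 365 mean. Ratios to the completers' variance, with effective n per arm in brackets, for correlation 0.8 down to 0.5:

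| Loss | Completers per arm | Equal correlation | AR(1) correlation |
|---|---|---|---|
| 0% | 75 | 1.000 (75) | 1.000 (75) |
| 20% | 60 | 0.857 to 0.931 (70.0 to 64.5) | 0.922 to 0.981 (65.1 to 61.2) |
| 30% | 52.5 | 0.784 to 0.895 (66.9 to 58.7) | 0.878 to 0.970 (59.8 to 54.1) |
| 40% | 45 | 0.711 to 0.858 (63.3 to 52.4) | 0.832 to 0.956 (54.1 to 47.1) |

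**4. Simulation.** 75 per arm, five visits, no true effect, 1,500 trials per scenario, normal outcomes. A likelihood model on all visits is compared with a last-visit regression on completers, both adjusted for baseline.

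- Random loss: variance ratio 0.92.
- Loss depending on the previous value in both arms: 0.97 and 0.89.
- Loss depending on the previous value in one arm only: variance ratios 0.95 and 0.94; bias of the completers' regression 0.072 and 0.083 SD, against 0.003 and −0.008 SD for the model; mean squared error ratios 0.77 and 0.73.

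The variance reduction is therefore 3% to 11%. Since √0.97 = 0.985 and √0.89 = 0.943, standard errors are about 1.5% to 6% smaller. A repeat with 600 trials per scenario and about 25% missing gave a reduction of 4% to 8%, a completers' bias of 0.084 SD, and a mean squared error 17% to 22% lower under one-arm loss.

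**The case against.** **The premise is partly an inference.** Section 2.12 ties only Visit 0 to the listed variables and otherwise says just that data are collected. A reader might infer that every quantitative outcome is measured at all five visits. That is reasonable but not stated, so the fix must be conditional on it.

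**Pooling is not planned.** Because no visit is named, a reader might infer that all visit records will be stacked as if they came from different people, with badly inflated false positives. Nothing in Section 2.13 says so. Separate tests at each visit are equally possible. No false-positive rate should be held against the plan.

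**A Day 365 regression is not unsound.** Adjusted for baseline, it is a standard analysis, valid if loss depends only on arm and the adjusted baseline covariates. It would be too strong to say that no reading of the plan is acceptable.

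**The gain is modest and assumed.** It vanishes without dropout. The bias figure belongs to loss that differs by arm; with the same mechanism in both arms and no true effect, symmetry gives no expected bias. Every scenario assumes missing at random, which favours the model; if unobserved relapse drives loss, neither method is protected. The normal simulation does not represent cigarettes per day, a count likely to have many zeros.

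**Some of this is analysis-plan detail.** The visit and the covariance structure often are. But the article itself commits to specific one-record methods and a firm rule against imputation, and it is that combination which discards the earlier values.

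All these limits on size and scope stand. None of them removes the central point.

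**Conclusion.** The concern holds as a recommended, inexpensive improvement and not as an error that invalidates the plan. On the 12-month reading, the named methods with no imputation amount to a completers' analysis of cigarettes per day, weight, BMI, blood pressure and heart rate. Given 25% to 29% loss and adjacent-visit correlation of 0.7 to 0.8, using the earlier visits lowers the variance by about 3% to 11%. It removes a bias of 0.07 to 0.08 SD if loss depends on earlier values in one arm only. Across the wider analytic range the variance reduction runs from about 2% (20% loss, AR(1), correlation 0.5) to about 29% (40% loss, equal correlation, 0.8). All loss and correlation figures are assumptions.

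The figures apply to roughly normal outcomes and are not shown for cigarettes per day. The simulation's comparator is a baseline-adjusted regression, so it does not measure the gain over the Wilcoxon test that the plan implies for the other four outcomes. A reader might infer that the trial's main result is at risk; it is not, since cessation, on which the sample size rests, is analysed separately.

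**What to change.** In Section 2.13, for the quantitative outcomes other than cessation:

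- Name the arm difference at Day 365 (Visit 6) as the reported contrast.
- State at which follow-up visits each outcome is measured.
- For weight, BMI, blood pressure and heart rate, estimate the contrast from a repeated-measures mixed model over those visits, with arm, visit, arm-by-visit, the Visit 0 value and an unstructured within-person covariance. Include everyone with at least one follow-up value.
- For cigarettes per day, use a longitudinal count model, or the same mixed model with robust standard errors plus a sensitivity analysis. Robust errors correct the variance but not a wrong likelihood under dropout.

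Leave the cessation analysis as it is. The change respects the rule against imputation and needs no new visits, data or participants. It costs wording and a little more programming. The model assumes that loss is explained by the observed values, which is weaker than what the completers' analysis assumes but still untestable. People with no follow-up value at all remain outside it, so the intention-to-treat statement should say so.

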### 2.9. Study Variables

The data collected will correspond to the following study variables, both outcome and explanatory.

Outcome variables will be: number of cigarettes smoked daily (discrete quantitative) *; smoking cessation (dichotomous): variable calculated on the basis of whether the number of cigarettes is equal to 0, and exhaled air CO-oximetry detects a value equal to or less than 10 ppm *; blood pressure (continuous quantitative); heart rate (continuous quantitative); weight in kilograms (continuous quantitative) *; and Body Mass Index (BMI) (continuous quantitative): variable calculated on the basis of weight and height) *.

Explanatory variables are sex (qualitative polychotomous); age (discrete quantitative); occupation (qualitative); postcode of residence (qualitative); cumulative smoking (discrete quantitative) *; and physical nicotine dependence measured by the Fagerström test [19] (discrete quantitative); psychological dependence, as measured by Glover Nilsson’s test [20] (discrete quantitative); motivation to quit smoking, as measured by the Richmond test [21] (discrete quantitative); weekly alcohol consumption (Standard Drinking Units-UBE) (discrete quantitative) *; World Health Organisation (WHO) Global Physical Activity Questionnaire (GPAQ) [22] and Benisovich’s physical activity self-efficacy scale [23].

(*) Some of the outcome variables can be considered intermediate variables of other explanatory variables, due to their causal relationship.

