## 3. Expected Results

The primary results will allow us to estimate the efficacy of prescribing physical exercise as an adjuvant therapy to classic multicomponent treatment, incorporating it as an additional element to be considered when it is accepted by the smoker. Secondly, we will find out, in young smokers, its acceptance as an optional therapy, with the high cost-effectiveness of quitting smoking as early as possible in the life of smokers.

We will also learn about the influence of the prescription of physical exercise in the female gender in relation to barriers such as weight gain and/or obesity, generally associated with smoking cessation. In addition to the potential added benefit in the control of associated dependent variables such as arterial hypertension, hyperglycaemia and dyslipidaemia, which are directly related to “physical inactivity” as an independent variable that is becoming increasingly relevant in our digital society.

The results obtained would be immediate, in terms of improving the smoker’s health, from the moment the smoking cessation process begins in synergy with the prescription of controlled physical exercise. We believe, therefore, that the results will affect the improvement in the level of health of smokers who achieve abstinence from smoking by improving their quality of life and, in the long term, their average life expectancy through the control of at least two risk factors such as smoking and physical inactivity. And not only to facilitate immediate smoking cessation but also to prevent craving and/or subsequent relapses, with a positive impact on the quality of life of people who achieve smoking cessation.

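### The Visit 0 value of each continuous outcome is collected but never named as a covariate, and for weight, BMI, blood pressure and heart rate the only named method that fits is an unadjusted Wilcoxon test

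*Protocol article*

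**What the plan says.** Section 2.9 lists six outcome variables: cigarettes per day, cessation, blood pressure, heart rate, weight and BMI. Cigarettes per day is a "number of cigarettes smoked daily (discrete quantitative") variable. The separate list of explanatory variables contains no baseline value of any of the five quantitative outcomes.

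Section 2.12 says of Visit 0: "Baseline data are collected on the previously mentioned variables". Baseline values of all the outcomes should therefore be available.

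Section 2.13 then assigns methods. For group comparison it says: "To compare groups by bivariate analysis, Wilcoxon, Chi-square or Fisher tests will be used, as appropriate". Regression is named for two outcomes only: logistic regression for cessation and "linear regression for the variable" number of cigarettes, in both cases "adjusting for potential confounders", with no list. It adds: "Further analyses, including sensitivity and subgroup analyses, will be conducted to explore the robustness and generality of the findings". It does not say whether the bivariate tests use follow-up values or changes from baseline.

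Section 3 expects the trial to show how prescribed exercise affects women in relation to "barriers such as weight gain and/or obesity". Sections 2.23 and 4 also present weight gain as something the intervention addresses.

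**The concern.** In a randomised trial the main reason to adjust for the baseline value of a continuous outcome is precision. A plan that justifies adjustment only by confounding does not ensure that the baseline value is included. For the four outcomes without a named model, the one stated method that fits makes no adjustment at all.

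Weight and BMI are the most exposed. Adults differ widely in weight at entry, and much of that spread is still there a year later. A direct comparison of 12-month weights carries all of it as noise. The trial also has little precision to spare: section 2.3 calculates 289 per arm for cessation and then settles on 75. An improvement that needs no further data is worth having.

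**Working it through.** The plan gives no precision or power figure for any continuous outcome, so there is none of its own to reproduce. The 289 per arm concerns cessation and does not enter here.

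**Inputs.** From the document: 75 per arm (section 2.3), power 80% (beta 20%) and alpha 5%. Assumed: a two-sided test (sidedness is not stated), the correlation r between Visit 0 and 12-month values, equal SDs at both times, and full follow-up. The document gives no SD or correlation, so results are in SD units over a range of r.

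**Formulas** for the detectable difference in SD units, with 1.960 + 0.842 = 2.802:
- follow-up values, unadjusted: 2.802 × √(2/75) = 0.458
- ANCOVA on baseline: 0.458 × √(1 − r²)
- change from baseline: 0.458 × √(2(1 − r))

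| r | Unadjusted | ANCOVA | Change score | Variance saved by ANCOVA against unadjusted |
|---|---|---|---|---|
| 0.3 | 0.458 | 0.436 | 0.541 | 9% |
| 0.5 | 0.458 | 0.396 | 0.458 | 25% |
| 0.7 | 0.458 | 0.327 | 0.354 | 49% |
| 0.9 | 0.458 | 0.199 | 0.205 | 81% |
| 0.95 | 0.458 | 0.143 | 0.145 | 90% |

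The unadjusted column is for a comparison of means. A simulation (2,000 runs per setting, normal data, true effect 0.2 SD) checked the Wilcoxon test itself on follow-up values. Its power was about 21–24% whatever r was. Baseline-adjusted regression had 24%, 29%, 41%, 80% and 97% at r = 0.3, 0.5, 0.7, 0.9 and 0.95.

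**In kilograms, assuming an SD of 15 kg:**
- unadjusted: 0.4575 × 15 = 6.86 kg
- ANCOVA: 4.12, 2.99 and 2.14 kg at r = 0.8, 0.9 and 0.95
- change score: 4.34, 3.07 and 2.17 kg at the same r

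If half the participants are women (also assumed), a comparison within women multiplies each figure by √2. The unadjusted one becomes 6.86 × 1.414 = 9.70 kg.

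**Cigarettes per day.** Entry requires at least 10 per day (section 2.4.1) and cessation requires zero (section 2.9). The outcome therefore has a spike at zero, which weakens its correlation with baseline. A second simulation assumed 10–30% quitters and a correlation of 0.5–0.9 among continuing smokers. The overall correlation was about 0.23–0.64. Adjustment lowered the variance by about 5–38% (8–24% at 20% quitters), with a ratio of adjusted to unadjusted standard error of 0.79–0.97.

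**Standard errors.** With n per arm in both arms, the pooled standard error of an unadjusted mean difference is √[((s₁² + s₂²)/2) × (2/n)] = √[(s₁² + s₂²)/n]. That equals the unequal-variance form, so a difference in spread between near-equal arms does little harm.

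**The case against.** The strongest reply is that the text leaves most of this open. The unlisted confounders could include baseline cigarettes, and no passage restricts adjustment to the explanatory list in section 2.9. Wilcoxon is not expressly assigned to weight, BMI, blood pressure or heart rate. Weight gain is itself a change from entry, and a test on changes would remove nearly all the loss for weight: 3.07 kg against 2.99 kg at r = 0.9. Covariate lists and models for non-cessation outcomes are often left to a fuller plan. The trial is a pilot aimed at cessation and makes no power claim for these outcomes.

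Much of this stands, and it rules out several stronger readings that a reader might infer:
- That the plan excludes baseline values. It only fails to name them.
- That baseline would enter only if it looked imbalanced. The text states no such rule.
- That a real effect on weight would be missed. This depends on comparing follow-up values, and the document gives no SD, correlation or expected effect.
- That much of the precision for cigarettes per day is thrown away. The gain there is mostly small to moderate, and any loss arises only if baseline is left out.
- That the ordinary least-squares confidence interval is wrong. With near-equal arms this is speculative.

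The argument from missing detail does not dispose of the point. Section 2.13 itself says which outcomes are modelled, and four of the five quantitative outcomes are not among them. Change scores would not be a general remedy either: at r = 0.5 they gain nothing, and at r = 0.3 they do worse than follow-up values alone.

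**Conclusion.** The point holds as a free improvement to the analysis; the plan contains no demonstrated error here. Two facts rest on the text alone: no baseline outcome value is named as a covariate anywhere, and the only named method that fits four continuous outcomes is an unadjusted test.

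The size is conditional on follow-up values being compared directly and on assumed correlations. It is large where r is near 0.9 or above, as may be expected for weight and BMI. It is moderate at 0.5–0.7, as might apply to blood pressure and heart rate, and modest for cigarettes per day. Losses to follow-up would raise all the detectable differences but leave their ratios unchanged. The cessation analysis is not affected. The change should be made, but the trial's main conclusion does not depend on it.

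**What to change.** State in section 2.13, or in the full analysis plan, that each continuous outcome is analysed by ANCOVA of the 12-month value on arm, its own Visit 0 value and the factors used to balance the arms (section 2.6, once these are named). Report the adjusted mean difference with its 95% CI. Keep Wilcoxon as a supportive test and say whether it uses follow-up values or changes. For cigarettes per day, heteroscedasticity-robust (HC3) or bootstrap standard errors are an optional safeguard because of the spike at zero.

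The cost is wording only. Visit 0 already collects the data, so no visit, measurement or participant is added. The wording should be fixed before outcome data are examined by arm.

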### 2.14. Bias Control

Selection bias will be controlled by applying the same selection criteria to the participants in the different groups to be compared, which will have identical monitoring. In addition, in the collection of information, a record of losses to follow-up will be kept, collecting as much information as possible about them. Regarding misclassification bias, smoking will be considered as a criterion of truth, the measurement of 6 or more ppm of CO in exhaled air by CO-oximetry. Finally, multivariate analysis using logistic regression will control for various confounding factors.

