### Limitations of the Project

This project should be seen in the context of its limitations. Firstly, the sample size could be an issue. However, the sample selected is representative of the study population, which is determined by the sample size, randomisation and selection criteria. Secondly, there is the possibility of losses during the course of the project, which is intended to be reduced by conducting an intention-to-treat analysis and by conducting follow-ups by telephone.

On the other hand, the project has the strengths of being a feasible, innovative and relevant study in terms of health gains, life expectancy, and the benefits in quality of life and well-being for people who meet the proposed objective by carrying out a programme that takes into account the quantity and quality of physical exercise performed [2]. We believe that the results obtained will be transferable to other countries where the same drug is dispensed and that the long-term results will be beneficial.

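### Intention-to-treat is combined with a ban on imputation and no rule for an undetermined 12-month outcome, so a literal analysis drops randomised participants

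*Protocol article*

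**What the plan says.** Section 2.13 sets one rule for every analysis: "All analyses shall be conducted on an intention-to-treat basis, and no missing data shall be imputed". The same section names logistic regression for smoking cessation, with Chi-square or Fisher tests for bivariate comparisons. It announces sensitivity and subgroup analyses in general terms and ties none of them to missing outcomes.

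Section 2.9 defines cessation as a "variable calculated on the basis of whether the number of cigarettes is equal to 0, and exhaled air CO-oximetry detects a value" of 10 ppm or less. Both conditions must hold. The 12-month assessment is in section 2.12: "Visit 6 (Day 365 ± 30): FACE-TO-FACE. Data are collected".

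Losses come up twice. Section 2.14 says that "a record of losses to follow-up will be kept, collecting as much information as possible about them". The limitations section says "there is the possibility of losses during the course of the project, which is intended to be reduced by conducting an intention-to-treat analysis", with telephone follow-up as the second means. No section assigns an outcome to a participant who is lost.

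**The concern.** The two halves of the rule in section 2.13 pull against each other. Intention-to-treat needs an outcome, or a principled treatment of its absence, for everyone randomised. A ban on imputation with no classification rule leaves some participants with a blank, and the named models drop blanks without comment. The result would carry the intention-to-treat label while using only those whose status was observed.

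This affects the 12-month cessation outcome in the trial's title. If participants who relapse are less likely to be seen at 12 months (an assumption, not something the documents state), the observed rate is too high in each arm. If the arms also lose different fractions, the comparison is biased. The arms differ in burden and contact: a leaflet on one side, a prescribed exercise programme with motivating calls on the other. Unequal loss is therefore possible. The limitations section relies on intention-to-treat as the protection against losses, and under this rule it gives none.

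**Working it through.** **Who is undetermined.** Take the two conditions of section 2.9 in turn.

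| Information at 12 months | Cigarettes = 0? | CO ≤ 10 ppm? | Status without imputation |
|---|---|---|---|
| Attends, both measured | known | known | determined |
| Reports smoking by telephone | no | not measured | not quit, because one condition has failed |
| Claims 0 cigarettes, no CO reading | yes | not measured | undetermined |
| Cannot be reached | unknown | unknown | undetermined |

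Only the last two rows are at issue. "Loss" below means the fraction of an arm in those rows.

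**Inputs.** From section 2.3: expected difference 3.18 points, delta 5 points, 75 per arm. The protocol gives no loss rate and no quit rate, so the plan has no figure of its own to reproduce on this point. Quit rates of 15% and 20% and the losses below are assumptions.

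**Formula.** Let q be the true quit rate in an arm, L its loss, and r the quit rate among those lost. The rate among those observed is (q − rL)/(1 − L). If everyone lost is smoking, r = 0 and this becomes q/(1 − L). If loss is unrelated to smoking, r = q and the rate is q, with no bias.

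**Equal loss, r = 0.** At q = 15% and L = 20%, 0.15/0.80 = 18.8%. The rate is inflated, but a zero difference stays zero. A non-zero difference is stretched: 17 against 15 quitters of 75 is 2.7 points, and with 60 observed per arm it becomes 2/60 = 3.3 points.

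**Unequal loss, r = 0, no true effect.**

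| q | Loss, arm 1 vs arm 2 | Observed rates | Spurious difference |
|---|---|---|---|
| 15% | 20% vs 15% | 0.15/0.80 = 18.8%; 0.15/0.85 = 17.6% | 1.1 points |
| 15% | 30% vs 15% | 0.15/0.70 = 21.4%; 0.15/0.85 = 17.6% | 3.8 points |
| 20% | 20% vs 15% | 0.20/0.80 = 25.0%; 0.20/0.85 = 23.5% | 1.5 points |
| 20% | 30% vs 15% | 0.20/0.70 = 28.6%; 0.20/0.85 = 23.5% | 5.0 points |

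The sign favours whichever arm loses more. Swapping the losses reverses it.

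**If the lost quit at half the overall rate** (q = 15%, r = 7.5%, loss 30% vs 15%): (0.15 − 0.0225)/0.70 = 18.2% and (0.15 − 0.01125)/0.85 = 16.3%. The bias falls to 1.9 points.

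**The opposite rule.** Suppose everyone lost is counted as smoking but loss is in fact unrelated to smoking, at 30% vs 15%. The spurious difference is 0.15 × (0.70 − 0.85) = −2.25 points at q = 15% and 0.20 × (0.70 − 0.85) = −3.0 points at q = 20%, against the arm that loses more.

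**The case against.** The best counter-argument is that section 2.9 already settles the matter. Cessation requires confirmation, so a participant without it does not meet the definition, and counting that person as a non-quitter derives the outcome and imputes nothing. The limitations section, which looks to intention-to-treat to deal with losses, fits that reading. It is a possible reading, but section 2.9 says nothing about absent measurements, and a ban on imputing any missing data points the other way. Two analysts could follow the text and report different primary results.

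The size is also open to challenge. The losses are assumed, the 1.1-point scenario is well below 3.18, and with 75 per arm the standard error of the difference is √(2 × 0.15 × 0.85/75) = 5.8 points at a 15% quit rate, larger than the bias shown. That stands as a limit on magnitude. It does not excuse a rule that departs from its own label, since bias does not average out as sampling error does.

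Two stronger inferences should be resisted. A reader might conclude that anyone reached only by telephone has no outcome. That is wrong: a person who reports smoking fails the zero-cigarette condition without a breath test. A reader might also conclude that the demanding exercise programme will lose more non-quitters and so produce a false benefit. The documents do not support a direction. Section 2.11.1 plans motivating calls to encourage adherence, section 2.23 expects the prescription to bring close follow-up, and section 2.14 promises identical monitoring. Retention could be better in the exercise arm.

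The design of sensitivity analyses can be left to a separate analysis plan. The primary rule cannot, because this document has already fixed it.

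**Conclusion.** The point holds. As written, section 2.13 calls for intention-to-treat, forbids imputation, and leaves participants of undetermined status unclassified. Applied literally, the cessation analysis excludes them and is not by intention to treat.

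Inflation by 1/(1 − loss) in each arm, and bias from unequal loss, follow only if those lost mostly smoke. With no true effect and a 15% quit rate, the illustrated bias is 1.1 to 3.8 points, from about a third of the expected difference to more than all of it. At a 20% quit rate the wider gap in loss reaches the delta of 5. These figures show what the rule permits. They do not predict what this trial will see, and either arm could be favoured. An inflated or biased result is a risk that the wording leaves open, not an established outcome.

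The point is confined to the cessation outcome. How cigarettes per day, weight or blood pressure are modelled is a separate choice.

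**What to change.** In section 2.13, replace the blanket ban, for the cessation outcome, with a rule that all randomised participants stay in the denominator of their allocated arm and that anyone without CO-verified abstinence at Visit 6 is counted as smoking. Add one sensitivity analysis on that assumption, either multiple imputation from earlier visits or a tipping-point analysis by arm. The present ban would rule out the first of these. Report loss by arm.

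In the limitations section, remove the statement that an intention-to-treat analysis reduces losses. Telephone follow-up may reduce them; an analysis principle cannot.

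The cost is a protocol amendment (section 2.18 requires ethics committee authorisation) and a small amount of extra analysis code, with no additional participants or visits. Reported quit rates will be lower. Counting the missing as smoking has its own bias when loss is unequal and unrelated to smoking, about −2.3 to −3.0 points at 30% vs 15% loss, which is why the sensitivity analysis has to accompany it.
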